**ADMINISTRATIVE INFORMATION**

**Registered at:** https://clinicaltrials.gov/ct2/show/NCT03965780

**Protocol available at:** https://trialsjournal.biomedcentral.com/articles/10.1186/s13063-019-3747-z

**SAP Version 1 (2021-06-14)**

**Study Design**

The SPIN-SSLED Trial is a pragmatic, two-arm, parallel, blocked, partially nested randomised controlled trial (PN-RCT). The trial is a blocked PN-RCT because eligible participants will first be grouped into blocks (referred to as “pools” in main text) based on language and scheduling availability, and then randomised into intervention arm. Within each block, participants randomised to the intervention arm will interact with their group facilitator and with others in their group during videoconference sessions. Within each block, participants randomised to the waitlist control arm will not interact with each other and will only complete trial measures.

**Study Outcomes**

The primary outcome analysis will compare self-efficacy (Scleroderma Support Group Leader Self-efficacy Scale [SGLSS]) scores between participants randomly assigned to the SPIN-SSLED Program versus the waitlist control at the end of the 13-week intervention period.

Secondary outcomes will include (1) SGLSS scores 3 months post-intervention; (2) burnout, measured by the Oldenburg Burnout Inventory (OLBI) post-intervention and 3 months post-intervention; (3) leader satisfaction that leading a support group is helping others, measured by the Participation Efficacy subscale of the Volunteer Satisfaction Index (VSI) post-intervention and 3 months post-intervention; and (4) emotional distress, measured by the Patient Health Questionnaire-8 (PHQ-8) post-intervention and 3 months post-intervention.

**Sample Size**

We identified several meta-analyses that have evaluated self-efficacy in terms of knowledge acquisition and confidence in implementing skills acquired in training programs. A 2016 Cochrane review reported a standardized mean difference effect size of 0.87 for 4 educational interventions designed to change knowledge of sickle cell disease among patients and caregivers (standardized mean difference = 1.12 with an outlier study removed).^1^ Several other similarly focused meta-analyses have reported effect sizes of between 0.58 and 0.94.^2-5^ In the SPIN-SSLED non-randomised feasibility trial, which only included 10 participants, the pre-post change in self-efficacy for carrying out leadership tasks was 1.7 standard deviations.^6^ For an assumed effect size of 0.70, a two-tailed test with α = 0.05, and an intra-class correlation coefficient (ICC) of 0.05, N = 75 would provide ≥ 80% power for self-efficacy for carrying out leader tasks. There was no loss to follow-up in our feasibility trial. Assuming 20% loss to follow-up in the proposed trial, we would need to randomise 94 support group leaders. We believe that this is a conservative power and sample size estimate. First, based on existing systematic reviews and on results of our feasibility trial, we believe that the true effect size is likely larger than 0.70. Second, in cluster RCTs, ICC values for individual patient outcomes are typically lower than our 0.05 estimate, even when different interveners are involved,^7-9^ and we will use the same trainer across groups in each language. If the true ICC is lower than our 0.05 estimate, this will result in greater power than estimated. Third, there was no loss to follow-up in our feasibility trial, and in our previous completed studies in SSc that required follow-up, loss to follow-up has been 10% or less.^10,11^

For the secondary outcomes (emotional distress, burnout, leader satisfaction (participation efficacy)), based on published meta-analyses, a standardized mean difference effect size of 0.50 represents a clinically meaningful effect size for improvement that has been achieved in training programs for managers, caregivers of chronically ill patients, and parents of children with difficult behavior.^2,12-14^ This is also considered a clinically meaningful effect size for patient-reported health outcomes, including depressive symptoms.^15^ For effect size = 0.50, a two-tailed test with α = 0.05, and an ICC of 0.05, N = 146 would provide ≥ 80% power for both self-efficacy and patient-reported health outcomes. Assuming 20% loss to follow-up in the proposed trial, we would need to randomise 182 support group leaders. We did not estimate power for leader satisfaction.

Members of our Support Group Leader Advisory Team and our patient organization partners have emphasized the importance of evaluating the trial’s planned secondary outcomes. Thus, we will attempt to enrol 180 participants total (15 training groups of 6 participants; 90 participants in waitlist control) in order to have sufficient power to adequately evaluate secondary outcomes.

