2. Analyses of secondary outcomes will similarly be done (1) controlling for baseline scores only and (2) controlling for baseline scores and additional covariates. However, OLBI and VSI were only collected and will only be assessed among experienced leaders, since they are not relevant to candidate leaders. Thus, these analyses will not include leader experience as an additional covariate.
3. To aid in the interpretation of study results, for primary and secondary outcomes, post-intervention and 3 months post-intervention, we will produce model-adjusted standardized mean differences (Hedges’ g), using an adapted version of the method proposed by Borenstein and Hedges.^20^ For each outcome and time point, we will calculate the associated Hedges’ g estimate by dividing the unstandardized regression coefficient for the intervention effect by the unadjusted standard deviation of the outcome variable. To produce standard errors, we will use formula 11.31 from Borenstein and Hedges, which incorporates an estimate of the proportion of unexplained variance in the model (i.e., “1 - R^2^” in a standard linear regression model).^20^ In our case, we will estimate this proportion by dividing the estimated residual variance from the model by the unadjusted variance of the outcome variable. Estimated Hedges’ g and associated standard errors will be computed in each imputed dataset and then results will be pooled across imputed datasets using Rubin’s rules.^19^ Since the Borenstein and Hedges formula was not designed for the PN-RCT but was adapted, it approximates Hedges’ g and 95% CI.

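### The ≥ 80% power stated for the secondary outcomes counts all leaders, but burnout is analysed only in experienced leaders, so the figure does not carry over to burnout

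*SAP*

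**What the plan says.** In the SAP, Sample Size, the paragraph on secondary outcomes begins "For the secondary outcomes (emotional distress, burnout, leader satisfaction (participation efficacy)), based on published meta-analyses" and takes 0.50 as a meaningful effect. For that effect, with "a two-tailed test with α = 0.05, and an ICC of 0.05", it then says that "N = 146 would provide ≥ 80% power for both self-efficacy and patient-reported health outcomes". Allowing for 20% loss, the paragraph arrives at 182 to randomise and ends with "We did not estimate power for leader satisfaction". The next paragraph sets enrolment at 180 (15 training groups of 6, and 90 on the waitlist) "in order to have sufficient power to adequately evaluate secondary outcomes", with no outcome excepted in that sentence.

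Under Data Preparation and Analysis, in the item on secondary outcomes, the SAP says that "OLBI and VSI were only collected and will only be assessed among experienced leaders". The imputation paragraph of the same section shows that candidate leaders, who do not yet lead a group, are also enrolled. The SAP gives no expected number or share of either kind of leader.

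**The concern.** The power calculation and the burnout analysis use different populations. The 146 counts every analysable leader; the OLBI analysis drops every candidate leader. No allowance for this enters the calculation.

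This matters because the secondary outcomes are the stated reason for enrolling 180, when Sample Size puts the need for the primary outcome at 94. A reader who meets an inconclusive burnout result and turns to the SAP would find a power figure that was not calculated for the population analysed.

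**Working it through.** **Inputs.** From Sample Size: effect 0.50 (0.70 for the primary outcome), two-sided α = 0.05, ICC 0.05, 20% loss, 180 enrolled 1:1, groups of 6. From Study Design: only the intervention arm is clustered. Not in the SAP, hence assumed: the share of experienced leaders (50% to 90% shown), their even split between arms, and the same loss among them.

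**Formula.** Design effect in the intervention arm: 1 + (6 − 1) × 0.05 = 1.25. With n per arm, SE² = (1.25 + 1)/n. Noncentrality δ = effect/SE. Power comes from the noncentral t distribution with N − 2 degrees of freedom.

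**Reproducing the plan.**
- N = 75, effect 0.70: SE² = 2.25/37.5 = 0.0600, δ = 2.86, power 80.5%.
- N = 146, effect 0.50: SE² = 2.25/73 = 0.0308, δ = 2.85, power 80.8%. The smallest N reaching 80% is 144.
- Loss: 146/0.8 = 182.5, against the stated 182.
- 180 × 0.8 = 144: SE² = 2.25/72 = 0.03125, δ = 2.83, power 80.2%.

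The plan's figures are sound for the full sample, with almost nothing to spare at 180.

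**Burnout, 20% loss.** Analysable N = 144 × share. Power is given twice: with the design effect held at 1.25, and with the group size reduced to the members analysed, m = 6 × 0.8 × share, so that the design effect is 1 + (m − 1) × 0.05. The last column is the effect with 80% power under the same two versions.

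| Experienced (assumed) | N | m | Design effect | Power at 0.50 | Detectable effect |
|---|---|---|---|---|---|
| 100% | 144 | 4.80 | 1.25 / 1.190 | 80.2% / 81.3% | 0.50 / 0.49 |
| 90% | 130 | 4.32 | 1.25 / 1.166 | 76% / 78% | 0.53 / 0.52 |
| 80% | 115 | 3.84 | 1.25 / 1.142 | 71% / 73% | 0.56 / 0.54 |
| 70% | 101 | 3.36 | 1.25 / 1.118 | 65% / 68% | 0.60 / 0.58 |
| 60% | 86 | 2.88 | 1.25 / 1.094 | 58% / 61% | 0.65 / 0.62 |
| 50% | 72 | 2.40 | 1.25 / 1.070 | 51% / 54% | 0.71 / 0.68 |

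Worked line, 80% with design effect 1.25: N = 115.2, SE² = 2.25/57.6 = 0.0391, δ = 0.50/0.1976 = 2.53, power 71%.

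**Share needed for 80% power.** About 139 (reduced groups) to 143 (design effect 1.25) analysable experienced leaders are needed.
- 20% loss (144 analysable): about 96.5% to 99.5% experienced.
- 10% loss (162): about 86% to 88.5%.
- No loss (180): about 77% to 80%.

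**Baseline adjustment.** The planned models adjust for the baseline score. With baseline correlation r, the variance is multiplied by roughly 1 − r², so 80% power is kept roughly when the experienced share is at least 1 − r² (75% at r = 0.5). With 20% loss, r = 0.5 and 80% experienced, power is about 83% to 84%. With r = 0.6 and 70% experienced it is about 83% to 86%; with r = 0.6 and 50% experienced, about 69% to 73%. The SAP states no correlation, so r is also an assumption.

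**The case against.** Several objections have force.

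- *Volunteer satisfaction.* A reader might infer that a stated 80% power fails for the VSI as well. It does not: the SAP says outright that it made no power estimate for leader satisfaction. What remains is narrower. The sentence justifying 180 speaks of the secondary outcomes without exception, and for the VSI nothing supports it.
- *Burnout is not named in the power sentence.* That sentence speaks of patient-reported health outcomes, and the example just before it is depressive symptoms. This is fair, but burnout is named at the head of the paragraph and leader satisfaction is the only outcome excepted, so the natural reading includes burnout.
- *20% loss is cautious.* Sample Size reports no loss in the feasibility trial and 10% or less in earlier studies. With 10% loss, a 90% experienced share would still give about 81% to 82%; an 80% share would give 76% to 78%. This shrinks the problem without removing it.
- *Baseline adjustment may restore the power.* It may, fully at some plausible values. But the stated figure takes no credit for it, so it cannot support that figure as written.
- *The denominator is disclosed.* The draft baseline table reports the number of experienced leaders and labels OLBI and VSI as restricted to current leaders, and Hedges' g with 95% confidence intervals will show the precision reached. This limits the harm of a misreading. It does not correct the power statement.

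**Conclusion.** The point holds for burnout. The ≥ 80% power was calculated on all leaders, while the OLBI analysis uses experienced leaders only. Under the SAP's own assumptions the figure would hold for burnout only if about 96.5% or more of participants were experienced. This is a mismatch of populations; the plan's arithmetic is correct for the full sample.

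The size of the shortfall cannot be fixed from the SAP. It runs from 2 to 4 points below 80% at a 90% experienced share to 26 to 29 points below at 50%, given 20% loss, an even split between arms and no credit for baseline adjustment.

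A reader might go further and conclude that the burnout analysis is in fact underpowered. The document does not support that, because the experienced share, the actual loss and the baseline correlation are all unknown, and favourable values could restore 80%. For the VSI the only defect is the unsupported general sentence about sufficiency. The primary outcome and PHQ-8 are unaffected, because both are analysed in all leaders.

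**What to change.** In Sample Size:

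1. Limit the ≥ 80% power statement to SGLSS and PHQ-8.
2. For OLBI, state the expected or actual number of experienced leaders, the resulting power at 0.50 and the detectable effect. If baseline adjustment is credited, state the correlation used and its source.
3. Reword the sentence justifying 180 so that its claim of sufficient power does not extend to OLBI or VSI.

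The cost is wording only: no change to enrolment, models or outcomes. The stated power for burnout would probably become less favourable.

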**Data Preparation and Analysis**

1. Data will be checked for completeness and cleaned
2. Descriptive Analyses:

- By arm (intervention vs waitlist), we will compare demographic and disease characteristics (see draft Table below)
- Participant reported satisfaction with the SPIN-SSLED Program post-intervention. The Client Satisfaction Questionnaire (CSQ-8) is an 8-item questionnaire evaluating user satisfaction. Items are scored on a 4-point Likert scale. Total scores range from 8 to 32, with higher scores indicating higher satisfaction with the service. Items have been modified slightly to refer to the SPIN-SSLED Program, as opposed to a generic service.

| **Variable** | **SPIN-SSLED Intervention** | **Waitlist** |
| --- | --- | --- |
| **Demographic** |  |  |
| Female sex, N (%) |  |  |
| Age in years, mean (SD) |  |  |
| Education in years, mean (SD) |  |  |
| Live in a city or town (versus suburb or rural), N (%) |  |  |
| Married or living as married (versus single), N (%) |  |  |
| Working full-time or part-time, N (%) |  |  |
| Country, N (%) |  |  |
| United States |  |  |
| Canada |  |  |
| Australia |  |  |
| New Zealand |  |  |
| United Kingdom |  |  |
| Other |  |  |
| Language of instruction, N (%) |  |  |
| English |  |  |
| French |  |  |
| Race/ethnicity, N (%) |  |  |
| White |  |  |
| Black |  |  |
| Hispanic/Latino |  |  |
| Other |  |  |
| **Disease characteristics** |  |  |
| Diagnosed with SSc, N (%) |  |  |
| Diffuse disease subtype among participants with SSc, N (%) |  |  |
| Years since SSc diagnosis among participants with SSc, mean (SD) |  |  |
| **Support group leader experience** |  |  |
| Experienced^a^ leader of SSc support group, N (%) |  |  |
| Years as a SSc support group leader among experienced leaders, mean (SD) (SD) |  |  |
| Works with a co-leader among experienced leaders, N (%) |  |  |
| Former regular member of their support group among experienced leaders, N (%) |  |  |
| **Patient-reported outcomes (baseline)** |  |  |
| Scleroderma Support Group Leader Self-Efficacy Scale, mean (SD) |  |  |
| Patient Health Questionnaire-8, mean (SD) |  |  |
| Oldenburg Burnout Inventory, among current leaders, mean (SD) |  |  |
| Volunteer Satisfaction Index, among current leaders, mean (SD) |  |  |

N = number of participants; SD = standard deviation; SSc = systemic sclerosis.

^a^Experienced leaders are participants who were already leading a support group at the time of trial enrolment.

1. Trial outcomes will be assessed pre-randomisation, immediately following the 13-week intervention, and 3 months after the end of the intervention period for both participants randomised to the intervention and participants randomised to waitlist.

All analyses will be conducted in R, and will be 2-sided, using an alpha value of 0.05. There will be no adjustment for the multiplicity of secondary outcomes.

For the primary outcome analysis (SGLSS post-intervention), we will use an intent-to-treat analysis that compares all participants randomly assigned to the SPIN-SSLED Program to all participants randomly assigned to the waitlist control. The intervention effect immediately post-intervention will be estimated using a linear mixed-effects model (using the lmer function in lme4),^16^ including baseline SGLSS scores as a fixed effect. To account for the clustering inherent to the blocked PN-RCT design, we will fit a random intercept and slope for intervention by randomisation block and an additional random slope for intervention-by-intervention cluster (i.e., participants in the intervention arm who were in a trial group with the same group leader).^17^

We will account for missing data by using multiple imputation by chained equations, using the mice package.^18^ We will generate 20 imputed datasets, using 15 cycles per dataset. Variables in the mice procedure will include: randomisation block, trial arm, number of intervention sessions attended, measures of all primary and secondary outcomes at all three assessment time points (baseline, post-intervention, and 3-months post-intervention), age, sex (female vs. male), years of education, living in a city or town (vs. suburb or rural), married or living as married vs. single, currently working full-time or part-time (vs. not currently working), Country (USA, Canada, UK, New Zealand, Australia, or Other), language of instruction (English vs. French), race/ethnicity (White, Black, Hispanic/Latino, or Other), whether the leader has SSc, diffuse vs. limited disease subtype (among those with SSc only), years since SSc diagnosis (among those with SSc only), whether the leader is an experienced (i.e., already leading a support group at the time of trial enrolment) vs. candidate (i.e., identified by a partner organization as intending to initiate a new support group) leader, years as a SSc support group leader (among experienced leaders only), whether leader works with a co-leader (among experienced leaders only), and whether the leader was formerly a member of their support group (among experienced leaders only). We will account for non-applicable responses (e.g., SSc related variables among participants without SSc) by using the “where” option in the mice package. For all outcome measures, we will use total scores rather than item scores, with one exception; for VSI scores at baseline, we will use the 7 items separately. This is because, due to a programming error at the beginning of the trial, several participants only completed 6 of the 7 items. Pooled standard errors and associated confidence intervals will be estimated using Rubin’s rules.^19^

1. As a secondary analysis of the SGLSS, we will also control for age (years), sex (male vs. female), whether the leader has SSc (no vs. yes), and whether the leader is an experienced leader candidate leader as fixed effects.
2. Analyses of secondary outcomes will similarly be done (1) controlling for baseline scores only and (2) controlling for baseline scores and additional covariates. However, OLBI and VSI were only collected and will only be assessed among experienced leaders, since they are not relevant to candidate leaders. Thus, these analyses will not include leader experience as an additional covariate.
3. To aid in the interpretation of study results, for primary and secondary outcomes, post-intervention and 3 months post-intervention, we will produce model-adjusted standardized mean differences (Hedges’ g), using an adapted version of the method proposed by Borenstein and Hedges.^20^ For each outcome and time point, we will calculate the associated Hedges’ g estimate by dividing the unstandardized regression coefficient for the intervention effect by the unadjusted standard deviation of the outcome variable. To produce standard errors, we will use formula 11.31 from Borenstein and Hedges, which incorporates an estimate of the proportion of unexplained variance in the model (i.e., “1 - R^2^” in a standard linear regression model).^20^ In our case, we will estimate this proportion by dividing the estimated residual variance from the model by the unadjusted variance of the outcome variable. Estimated Hedges’ g and associated standard errors will be computed in each imputed dataset and then results will be pooled across imputed datasets using Rubin’s rules.^19^ Since the Borenstein and Hedges formula was not designed for the PN-RCT but was adapted, it approximates Hedges’ g and 95% CI.

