**Amendments to Statistical Analaysis Plan**

1. The mice procedure needed to be modified to run successfully. We removed randomisation block, intervention arm, whether the leader has SSc, and whether the leader is an experienced versus candidate leader from the list of variables included in the mice procedure, as these variables were collinear with other variables included in the mice procedure. We also did not use the ‘where’ option to account for non-applicable responses, as this was not possible after removing these variables from the mice procedure. Instead, we re-set non-applicable values to ‘NA’ after the mice procedure was completed.
2. For the primary outcome (SGLSS scores immediately post-intervention), the intended analytical models did not converge. Thus, these analysis models were simplified to remove random slopes and to only include a single random intercept for each separate intervention group and for all waitlist participants combined (i.e., not separated by randomisation block) to facilitate convergence.

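### As amended, the multiple imputation omits both training group and block, so it shrinks the group variance that the analysis model estimates; the effect on the SE is small at the assumed ICC

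*SAP*

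**What the plan says.** **Why outcomes cluster.** SAP, Study Design: within each block, "participants randomised to the intervention arm will interact with their group facilitator and with others in their group". Waitlist participants do not interact.

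**Analysis model as planned.** SAP, Data Preparation and Analysis: "To account for the clustering inherent to the blocked PN-RCT design", the model has a random intercept and slope by block and "an additional random slope for intervention-by-intervention cluster".

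**Analysis model as amended.** SAP, Amendments, item 2: because of non-convergence, the primary-outcome models now "only include a single random intercept for each separate intervention group and for all waitlist participants combined". Item 2 names the primary outcome only.

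**Imputation as planned.** SAP, Data Preparation and Analysis: "Variables in the mice procedure will include: randomisation block, trial arm, number of intervention sessions attended", then all outcomes at the three time points and demographic, disease and leadership variables. There are 20 datasets, pooled by Rubin's rules. No training-group identifier is listed and no multilevel method is named.

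**Imputation as amended.** SAP, Amendments, item 1: "We removed randomisation block, intervention arm, whether the leader has SSc, and whether the leader is an experienced versus candidate leader", the reason being "as these variables were collinear with other variables included in the mice procedure".

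**The concern.** Multiple imputation followed by a mixed model works well when the imputation model contains the structure that the mixed model estimates. Here, after the amendment, it does not. For the primary outcome, the only clustering modelled within the intervention arm is the training group, a factor that the imputation never uses. For the secondary outcomes, the SAP as written keeps both block and group random effects, and neither is in the imputation.

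An imputed intervention participant is then close to an independent draw. The completed data show less within-group correlation than the real data, and the group variance is estimated too low. If that variance drives the SE, the SE falls too. This is a separate matter from the removal of trial arm, and would remain if arm were put back.

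**Working it through.** **Inputs.** From the SAP, Sample Size: effect sizes 0.70 and 0.50, two-sided alpha 0.05, power 80%, ICC 0.05, 20% loss, 15 groups of 6 and 90 waitlist. Also from there: loss of 10% or less in earlier studies. Assumed here: ICCs of 0.10, 0.15 and 0.20 as higher scenarios, total outcome variance of 1, and outcomes missing completely at random.

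**Step 1: the SAP's own figures.** The SAP gives no figure for the imputation, so the check is on its use of the ICC. The design effect in a group of 6 is 1 + (6 − 1) × 0.05 = 1.25. Applied to the intervention arm only, the average is (1.25 + 1)/2 = 1.125.
- Effect size 0.70: 33 per arm (normal) or 34 (t) gives 66 × 1.125 = 74.25 or 68 × 1.125 = 76.5, against 75 stated. Then 75/0.8 = 93.75, so 94, as stated.
- Effect size 0.50: 126 × 1.125 = 141.75 or 128 × 1.125 = 144, against 146 stated. Then 146/0.8 = 182.5, against 182 stated.

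The figures fit clustering in the intervention arm alone, so the training-group variance is the right quantity to follow.

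**Step 2: expected shrinkage.** Two members of a group keep their correlation only if both are observed. With a fraction p missing and no group information in the imputation, apparent ICC ≈ ICC × (1 − p)². The complete-data SE ratio is √[(2 + 5 × apparent ICC)/(2 + 5 × ICC)].

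| True ICC | Loss | Apparent ICC | Intervention-arm design effect | SE ratio |
|---|---|---|---|---|
| 0.05 | 10% | 0.0405 | 1.25 → 1.203 | 0.989 |
| 0.05 | 20% | 0.032 | 1.25 → 1.16 | 0.980 |
| 0.10 | 20% | 0.064 | 1.50 → 1.32 | 0.963 |
| 0.15 | 20% | 0.096 | 1.75 → 1.48 | 0.950 |

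The proportion lost is 1 − 0.8² = 36% at 20% loss and 1 − 0.9² = 19% at 10%. The pooled SE moves less than the last column because Rubin's rules add between-imputation variance.

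**Step 3: simulation.** 15 groups of 6, 90 waitlist, 20% missing, 20 imputations, arm kept in the imputation to isolate this fault. The comparator is REML on the observed data.

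| True ICC | Mean ICC, observed data | Mean ICC, single-level imputation | Change in ICC | Change in SE |
|---|---|---|---|---|
| 0.05 | 0.057 | 0.042 | −26% | about −1% |
| 0.10 | 0.089 | 0.063 | −29% | about −2% |
| 0.20 | 0.156 | 0.107 | −31% | about −3% to −4% |

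The observed-data column itself departs from the true ICC, so the fair comparison runs along each row. A separate simulation with an ANOVA variance estimator agrees with step 2. At 20% loss, ICC 0.05 appears as 0.031 and 0.15 as 0.093; at 10% loss, 0.05 appears as 0.0425. Replacing arm by sessions attended made no difference (0.032 either way at ICC 0.05 and 20% loss).

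Type I error over 2,500 simulated trials was 5.6% / 6.5% / 7.2% at ICC 0.05 / 0.10 / 0.20 after imputation, against 5.2% / 6.1% / 6.0% from observed-data REML. The Monte Carlo SE is about √(0.05 × 0.95/2500) = 0.44 points, so the difference at 0.05 is within noise.

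**Step 4: the list before the amendment.** If each block held one training group (not stated outright), then with block and arm as main effects, ICC 0.05 and 20% loss, the ICC appeared as 0.08. The ratio of SE to true sampling SD was 1.08, against 1.02 for complete data in the same run. That is overstatement.

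**Step 5: the amended primary model.** Treating the whole waitlist as one random-intercept cluster adds a full group variance τ² to the variance of the contrast. At ICC 0.05 with no missing data, the proper variance is 2.25/90 = 0.025. Adding 0.05 gives 0.075, and √(0.075/0.025) = 1.73. Averaged over simulated trials, the SE was about 1.9 times the true SD without missing data and about 1.6 times after single-level imputation at 20% loss. The inflation arises only where the group variance is estimated above zero; it was zero or below in about 37% of imputed datasets at ICC 0.05.

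**The case against.** The strongest reply is that nothing of consequence follows at the SAP's own values. At ICC 0.05 and 20% loss the ratio of pooled SE to sampling SD was 0.1756/0.1759 = 0.998. The SAP regards both values as cautious: it expects lower ICCs, uses the same trainer within each language, saw no loss in its feasibility trial and 10% or less in earlier studies. It plans no report of the ICC, so a biased ICC matters only through the SE. All this stands, and it limits the size of the point.

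A reader might infer that imputed intervention outcomes carry no group effect at all. The documents do not support that. Before the amendment, block and arm could carry part of it (step 4). After it, the other outcomes, the 3-month scores and sessions attended can still carry a little.

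A reader might also infer that the reported primary confidence interval is too narrow and its type I error too high. That is not established either, because the single waitlist cluster can push the SE the other way, by more (step 5). But this does not dispose of the point: the offset vanishes where the group variance is estimated at zero, item 2 does not extend the simplified model to the secondary outcomes, and two errors of opposite sign do not make a valid analysis.

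Finally, the imputation already failed once with the planned list, and groups are smaller still for the burnout and satisfaction scores, which cover experienced leaders only. That is a fair caution about the remedy.

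**Conclusion.** The point holds for the amended imputation. It leaves out the training group and the block while the analysis models estimate training-group clustering, and it biases the group variance toward zero: by roughly a quarter to a third at 20% loss, and by about 19% at 10%. At ICC 0.05 the pooled SE falls by about 1%, with no clear type I error inflation. At assumed ICCs of 0.10 to 0.20 it falls by about 2% to 4%. The point does not extend to the list before the amendment. For the primary outcome, the direction of the net SE error also depends on the single waitlist cluster.

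The figures rest on 15 groups of 6, outcomes missing completely at random, and no help from auxiliary variables that carry group information. They would be smaller if such variables helped. This is worth correcting because the check is cheap, not because it overturns the primary analysis.

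**What to change.** Impute the two arms separately. In the intervention arm use a two-level method with the training group as cluster (for example 2l.pan in mice); in the waitlist arm use the single-level method. Separate imputation also removes the need for arm as a predictor, which the amendment dropped as collinear. In simulation the two-level method restored the ICC and the SE, slightly conservatively and depending on the prior.

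Do not enter the groups as fixed dummies. At ICC 0.05 and 20% loss that made the ICC appear as about 0.14 and the SE about 14% larger than the true sampling SD (complete data in the same run: 2% larger).

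At a minimum, fit a partially nested model by REML to the observed outcomes, with a random training-group effect in the intervention arm and none in the waitlist, and report it beside the imputed result for each outcome and time point.

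**Cost.** The REML fit is nearly free, but it does not use the auxiliary variables, and incomplete baseline satisfaction scores would still need handling. With 15 small groups, the two-level imputation needs a trimmed predictor set and a stated prior, and may be slightly conservative. The amendment is worded in the past tense, so the imputation appears to have been run already; both steps can then be added as declared sensitivity analyses.
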